#### Confidentiality

Lists containing all patients with a diagnosis of MS will be collected from the MS outpatient clinics. These lists will be sent via email as password-encrypted files, and the passwords will be sent separately as text messages. Members of the study group will screen the lists against the inclusion and exclusion criteria through access to the hospital journals. Each participant will be assigned a study ID, and only the study ID will be entered into the study database. A key connecting the study ID to the participant’s name will be stored separately in the secure study database and will only be accessible to two members of the study group.

#### Analysis

First, the study aims to generate new knowledge regarding the short- and long-term effects of the CoreDISTparticipation intervention compared to usual care on barriers to work, physical activity, balance, walking, fatigue, and HRQoL in employed individuals with minor-to-moderate disability due to MS. As the intervention is complex and comprises several elements, the study will investigate the overall effects. The variables examined are well-known barriers to work and quality of life in this population [30]. Understanding the relationships between these and the intervention’s potential effects will provide valuable knowledge for further development of follow-up care.

Second, this study will provide objective information about health economic factors related to pwMS with low disability. This includes the utility of the CoreDISTparticipation program compared to usual care, expressed in QALYs, long-term employment status, and work-related costs. Given the high work-related costs associated with pwMS [4,7], this study will offer essential insights to further develop follow-up care and potentially enhance workforce sustainability for this group. Thus, the study addresses the part of the follow-up that represents the highest societal costs for pwMS in Norway [4].

#### Data Analysis

Raw data from the ActiGraph wGT3x-BT monitors will be converted into categories of minutes of sedative time, minutes of light and moderate-to-vigorous physical activity, and the number of steps per day using ActiLife software. The raw platform data will be filtered using a fourth-order Butterworth filter at 10 Hz. Center of pressure (COP) data will be calculated using BalanceClinic software and exported to MatLab, where the root mean square (values) representing postural sway amplitude will be calculated. Multiple imputations of missing data in PROMs will be applied, when appropriate. EQ-5D-5L answers will be coded into digits according to the recommendations in the instrument handbook. Value sets representative for the Norwegian population will be used in the calculation of a single summary index value.

#### Statistical Analysis for Primary and Secondary Outcomes

##### Work Package 1

Intention-to-treat analysis using descriptive statistics and, when appropriate, mixed models will be used to determine possible between-group differences over repeated measurements. Descriptive statistics including graphical methods, nonparametric tests, correlation, and regression analyses will be performed.

##### Work Package 2

The EQ-5D-5L (from WP1) is the primary outcome measure used in this analysis, which will be supplemented with generic complementary questions. Responses from the EQ-5D-5L will be used to examine the overall net utility gain from the CoreDISTparticipation program compared to usual care. Cost utility analysis is a form of economic evaluation that uses quality-of-life measurements (eg, from the EQ-5D-5L) to compare the cost-effectiveness of different interventions.

A key indicator used in a cost utility analysis is QALY, a measure that combines the quantity and quality of health to calculate treatment outcomes that influence health. The cost per QALY for the two treatments will be modeled against work barriers to determine the relative costs and health benefits associated with each treatment. We will use the data from the study to develop a model to estimate the total costs and gains of the intervention in a lifetime perspective.

No interim analyses are planned. Subgroup analyses based on age, gender, the EDSS score, physical activity level at baseline, and geographical region will be performed, as appropriate.

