To address these issues, we have developed a comprehensive intervention entitled *CoreDISTparticipation*. This multidisciplinary follow-up is delivered across health care levels (hospitals and municipalities) and sectors (health and employment/welfare). It builds on the GroupCoreDIST exercise intervention [35], which addresses prerequisites for balance, such as dynamic trunk control and coordination within and between proximal (core) and distal bodily areas, delivered in small groups. These exercises emphasize high dose, dual task (D); individualization and new insights (I); somatosensory function optimization (S); and task-oriented training (T). GroupCoreDIST has proven effective for trunk control, balance, and walking in the short and the long term [12,13]; is a valuable tool for physiotherapists [36-38]; and enhances pwMS engagement in physical activity [39]. In addition, CoreDISTparticipation incorporates structured support from NAV consultants and employers, as well as digital support, and emphasizes outdoor physical activity. This innovative intervention has been investigated through a feasibility pilot RCT [31], a pretest-posttest feasibility study [32], and interviews [40]. Following minor adjustments, it is ready for a large-scale RCT. Currently, there is a scarcity of evidence regarding proactive comprehensive interventions addressing function, health, and work in pwMS. The trial presented in this protocol will investigate the effectiveness and cost-effectiveness of the new intervention.

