## Methods

### Trial Design

This study consists of two WPs. WP1 is a parallel, two-arm prospective, single-blinded, multicenter RCT with an allocation ratio of 1:1 to investigate whether CoreDISTparticipation is superior to usual care in terms of reducing barriers to work and improving physical activity levels, physical functions, and HRQoL. The study is registered at ClinicalTrials.gov (NCT06110468). WP2 aims to determine the utility of the CoreDISTparticipation intervention in terms of HRQoL and quality-adjusted life-years (QALYs), employment status, and work-related costs when compared to usual care. The trial protocol is reported in line with the SPIRIT (Standard Protocol Items: Recommendations for Interventional Trials) checklist (Multimedia Appendix 1) and the CONSORT statements for reporting RCTs.

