#### Work Package 2 (Utility Study)

The outcomes for WP2 will be the net utility gain, employment status, and cost utility (Table 5). Data related to participation in work will be obtained cross-sectionally at baseline in WP1 and after week 52 through self-registration and linkage to the NAV register. The participants will provide information about the type and number of follow-ups and treatments from the physiotherapist, the general practitioner, the neurologist, and the NAV consultant in digital questionnaires distributed from REDCap. From the NAV registry, data will be obtained for the following variables: work status, sick leave, WAA and disability benefits, family-related leave (ie, maternity leave), pension, social aid, and unemployment benefits.

**Table 5 table5:** Outline of outcomes for WP^a^2.

Outcome	Description
Net utility gain: QALYs^b^	QALYs will be calculated for both groups using EQ-5D-5L scores from WP1.
Employment status	The status for and changes in employment will be calculated based on self-reports and registry data from NAV^c^. To enable calculation of long-term effects, we will gather data on the aforementioned variables 1 year after the intervention.
Cost utility	Data on treatment costs will be obtained from the tariffs and weights used in municipal and specialist health care.

^a^WP: work package.

^b^QALY: quality-adjusted life-year.

^c^NAV: Norwegian Labour and Welfare Administration.

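### The cost-utility measure is worded as a cost per QALY for each arm, modelled against work barriers; it should be incremental cost combined with the planned incremental QALYs

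*Protocol article*

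**What the plan says.** The Background section promises a trial that "will investigate the effectiveness and cost-effectiveness of the new intervention". Trial Design sets Work Package 2 (WP2) as a comparison of utility, "employment status, and work-related costs when compared to usual care". Table 5 lists the inputs: "QALYs will be calculated for both groups using EQ-5D-5L scores from WP1", under a row labelled as net utility gain, and "Data on treatment costs will be obtained from the tariffs and weights used in municipal and specialist health care".

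The WP2 part of the statistical analysis section then makes four statements:

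- On the effect side: "Responses from the EQ-5D-5L will be used to examine the overall net utility gain from the CoreDISTparticipation program compared to usual care".
- On purpose, cost-utility analysis serves "to compare the cost-effectiveness of different interventions".
- On the measure itself: "The cost per QALY for the two treatments will be modeled against work barriers to determine the relative costs and health benefits" of each treatment.
- On extrapolation, with a lifelong horizon: "We will use the data from the study to develop a model to estimate the total costs and gains of the intervention in a lifetime".

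The third statement is the only one that says how costs and QALYs will be put together. The article names no incremental cost-effectiveness ratio, net benefit or willingness-to-pay threshold. A between-arm comparison of work-related costs is an aim, but no cost difference is combined with the QALY difference.

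**The concern.** Whether one option is cost-effective relative to another depends on the extra cost set against the extra QALYs. A cost per QALY for each treatment divides each arm's total cost by its total QALYs. Comparing two such ratios answers another question and can point the other way.

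Relating the ratio to work barriers adds a second difficulty. Work barriers are measured by the MSWDQ-23NV, a primary outcome of Work Package 1 (WP1), and the Objectives section hypothesises that the intervention will improve them. If post-baseline values enter as a covariate, the contrast conditions on something that treatment may have changed. If they enter as a denominator, the result is no longer a cost per QALY. The sentence does not say which role is meant, or which visit supplies the values.

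The health economic evaluation is in the article's title. The article expects a low-cost programme, yet it also warns of a possible early rise in sick leave costs. The cost difference between arms, and how it is weighed against health gain, is therefore central to WP2.

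**Working it through.** There is no health-economic figure in the article to reproduce, so the check is algebraic. **Every cost, QALY and threshold below is an assumption chosen for illustration.**

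**Definitions.** Let C and Q be mean cost and mean QALYs, with 0 for usual care and 1 for the intervention.

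- Average ratio in arm k: C_k / Q_k
- Incremental ratio: (C1 − C0) / (Q1 − Q0)
- Incremental net benefit at threshold λ: λ(Q1 − Q0) − (C1 − C0)

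**Step 1: what ranking by average ratios implies.** Suppose Q1 > Q0. Then C1/Q1 < C0/Q0 is the same as C1 < C0·Q1/Q0. Subtracting C0 gives C1 − C0 < (C0/Q0)(Q1 − Q0), so the incremental ratio is below C0/Q0. Ranking the arms by average ratio therefore sets the threshold at usual care's own average cost per QALY, which has no standing as a decision threshold.

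**Step 2: the ranking can reverse in either direction.** Assumed λ = NOK 300,000.

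- *Intervention looks worse but has positive net benefit.* Usual care 20,000/0.75 = 26,667; intervention 22,000/0.77 = 28,571. Incremental ratio 2,000/0.02 = 100,000. Net benefit 300,000 × 0.02 − 2,000 = +4,000.
- *Intervention looks better but has negative net benefit.* Usual care 750,000/0.75 = 1,000,000; intervention 758,000/0.76 = 997,368. Incremental ratio 8,000/0.01 = 800,000. Net benefit 300,000 × 0.01 − 8,000 = −5,000.

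When Q1 > Q0, net benefit is positive exactly when λ exceeds the incremental ratio. Both reversals therefore hold at any threshold between NOK 100,000 and 800,000.

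**Step 3: the same two average ratios fit opposite decisions.** Hold them at NOK 100,000 (usual care, Q0 = 0.75, so C0 = 75,000) and NOK 105,000 (intervention, so C1 = 105,000 × Q1).

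| Q1 | C1 − C0 | Q1 − Q0 | Incremental ratio | Net benefit, λ = 200,000 | λ = 300,000 | λ = 500,000 |
|---|---|---|---|---|---|---|
| 0.74 | 2,700 | −0.01 | dominated | −4,700 | −5,700 | −7,700 |
| 0.76 | 4,800 | 0.01 | 480,000 | −2,800 | −1,800 | +200 |
| 0.77 | 5,850 | 0.02 | 292,500 | −1,850 | +150 | +4,150 |
| 0.78 | 6,900 | 0.03 | 230,000 | −900 | +2,100 | +8,100 |
| 0.80 | 9,000 | 0.05 | 180,000 | +1,000 | +6,000 | +16,000 |
| 0.85 | 14,250 | 0.10 | 142,500 | +5,750 | +15,750 | +35,750 |

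At each threshold the sign of net benefit changes down the column while the two average ratios stay the same.

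**Step 4: can the planned data give the right quantities?** Yes. The Outcomes section and Table 4 schedule the outcome measures, including EQ-5D-5L, at baseline and weeks 9, 16 and 52. (The abstract lists visits only to week 16.) Table 5 plans QALYs for both groups and treatment costs.

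**The case against.** The fairest defence is that the sentence is loose shorthand in a condensed article. The same section plans a net utility gain compared with usual care, which is an incremental QALY, and Table 5 labels the outcome that way. Costs and QALYs by arm are planned, as is a lifetime model of costs and gains, so the incremental quantities follow from data in hand. A separate health-economic plan may state them.

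Much of this stands, and it rules out several stronger readings that a reader might infer:

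- *That incremental QALYs have been dropped.* They have not; the net utility gain is planned. What is missing is a cost difference combined with it.
- *That the trial cannot show cost-effectiveness.* The stated measure does not show it, but the planned data would permit the right analysis.
- *That the analysis certainly conditions on a post-randomisation variable.* The role and timing of work barriers are not stated, and the MSWDQ-23NV is also measured at baseline. The objection applies only if post-baseline values are used.
- *That QALYs will be compared without baseline adjustment.* The article is silent, and covariates can properly be left to an analysis plan.

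The defence does not remove the core point. This is a measure the article states, not a detail it leaves out. It is the only sentence that combines cost with QALYs, and taken literally it combines them wrongly for the declared purpose.

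**Conclusion.** The point holds as a fault in the stated measure. As written, the cost-utility result is an average ratio per arm. It does not determine the incremental cost per QALY gained and can disagree with net benefit in either direction. Linking it to work barriers leaves the estimand unclear, and would move it away from the randomised cost-QALY comparison if post-baseline values serve as covariate or denominator.

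The algebra in step 1 needs no trial data. The illustrated sizes, such as an incremental ratio between NOK 142,500 and 480,000 from one pair of average ratios, rest wholly on assumed inputs and do not predict this trial's result. The conclusion also assumes that the sentence means what it says; if it is shorthand for an incremental analysis, the remedy is the same rewording. Randomisation, data collection and the WP1 primary comparisons are not affected.

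**What to change.** Replace the sentence, before the economic analysis is run, with a statement to this effect:

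- Estimate incremental cost and incremental 52-week QALYs by randomised arm. Compute QALYs as the area under EQ-5D-5L utility (u) at weeks 0, 9, 16 and 52: [9(u0 + u9)/2 + 7(u9 + u16)/2 + 36(u16 + u52)/2] / 52.
- Combine the two as an incremental cost-effectiveness ratio and/or incremental net benefit, with uncertainty, for example from a bootstrap of cost-QALY pairs.
- Feed the lifetime model from these increments.
- Report work barriers as a separate outcome, not as a covariate or denominator of the cost-utility result.

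As a free refinement, adjust the QALY difference for the baseline EQ-5D-5L utility already collected. With an assumed utility SD of 0.10 to 0.20 and 115/2 = 57.5 participants per arm, the chance baseline gap has a standard error of SD × √(2/57.5), or 0.019 to 0.037. How far such a gap carries into the QALY difference depends on how persistent utility is over the year.

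The cost is plan wording and modest programming. No new data are needed.

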#### Analysis to Handle Protocol Nonadherence and Missing Data

The intention-to-treat principle will be applied to all analyses. Withdrawals from the study, loss to follow-up, and other missing data will be reported, as well as adherence to the intervention as attendance is monitored. In the case of missing data, multiple imputations may be performed, if appropriate.

### Oversight and Monitoring

#### Composition of the Coordinating Center and Trial Steering Committee

The Nordland Hospital Trust is the coordinating center for the trial where the Trial Management Group (TMG) works. The TMG consists of the chief investigator and three study co-investigators who are responsible for the setup of the study, the daily management of the trial, the development of study materials with relevant collaborators, promotion, data management, analysis, and dissemination. The Trial Steering Committee (TSC) consists of neurological consultants with trial experience, statisticians, health economists, quantitative researchers, user representatives, and people with expertise in neurological physiotherapy, cognitive and psychological disabilities in MS, and work adaptations. The TSC will conduct annual meetings to oversee the progress of the trial. Representatives from NAV and four user representatives have been involved in planning and promoting the study, as well as creating materials, such as information videos. The user representatives will take part in discussions throughout the project period, particularly regarding results and implications for practice. The user representatives have participated in both physical and digital meetings and play a central role in delivery of information to members of the MS Association, the MS population, and the general population. Throughout the project, they will find possibilities to impact the project and influence clinical practice within the field.

The study has no data monitoring committee as this is not mandatory for studies not investigating the effects of drugs or medical equipment.

#### Adverse Event Reporting

Any adverse events or harm to the participants during assessments or the intervention will be registered on a case record form and monitored by the TMG. The TMG will keep a log of any negative feedback from the participants. Any serious study-related adverse events will be reported to the regional ethics committee.

The TSC will monitor the progress of the study and adherence to the protocol.

#### Plans for Communicating Important Protocol Amendments to Relevant Parties

Any protocol amendments will be discussed in the TMG and will be made by the chief investigator, who will send any proposed amendments to the regional ethics committee and the data protection officer at the involved study sites for approval. ClinicalTrials.gov will be updated in the case of any major protocol changes. All participants will be notified via email in the case of protocol changes affecting their participation.

### Ethical Considerations

The study has received ethical approval from the Regional Committee for Medical and Health Research Ethics, North (REK-Nord 608117), and the data protection officers at the Nordland Hospital Trust, the University Hospital of North-Norway, the Finnmark Hospital, and the Helgeland Hospital. The study will adhere to the Declaration of Helsinki.

All eligible participants will receive a text message sent to their telephone containing a link to Nettskjema (online form provider) and the TSD’s secure solution for storing research data (developed and hosted by the University of Oslo) containing an information letter and the opportunity to provide consent. Participants will fill out a questionnaire with information about their employment status and digitally sign the consent form. At Nettskjema and TSD login, digital consent is interfaced with the governmental ID portal. The digital consent forms will be stored securely in the TSD database. The TSD is designed for storing and postprocessing sensitive data in compliance with the Norwegian Personal Data Act and Health Research Act. All participants and partners in the project will be treated with respect, and anonymity of participants will be undertaken.

All participants will provide consent to the publishing of anonymous results. No identifying images or other personal information of the participants will be presented. The information videos and exercise booklet contain films and images of models. They have consented to the materials being distributed, as described in the protocol, and in publications from the study. In the case of ancillary studies in the future, ethical approval and separate consent will be obtained.

Dissemination will be conducted in accordance with the Vancouver Protocol. At least two scientific papers will be published in peer-reviewed journals, and results will be presented at national and international meetings and conferences, such as the Norwegian Physiotherapy Association Congress, the World Congress for Physical Therapists, multidisciplinary congresses on MS (eg, Rehabilitation in MS); at meetings in Norwegian and local MS Associations; and in newspapers, podcasts, and websites.

## Results

The protocol is currently version 5 as of December 5, 2023. We completed the enrollment phase and enrolled and randomized 115 participants in two phases as of August 1, 2024. The 15-week retests were completed in December 2024, and data collection is estimated to be completed in September 2025. Results are expected to be published in the first quarter of 2026. An overview of the flow of participants through the study is presented in Figure 3.

**Figure 3 figure3:**
[figure not shown]
Overview of the flow of participants through the study.

## Discussion

### Summary

The study will investigate the effectiveness of CoreDISTparticipation, an innovative comprehensive intervention that is the first to integrate the health and welfare sectors by systematically and proactively addressing physical functions, physical activity, and work adaptations. The study includes employed pwMS with minor-to-moderate disability, a group whose vulnerability in terms of early withdrawal from the workforce is well documented [4,5,18,19,27]. During this stage of MS when disability is minor to moderate, the potential for a significant impact at both individual and societal levels is the greatest [17]. Our hypothesis is that compared to usual care, this comprehensive intervention will positively impact the barriers to work experienced, the levels of physical activity, and balance and dynamic trunk control, as well as HRQoL and health economic aspects, such as utility expressed in QALYs and employment status.

The principal findings of potential short- and long-term reduced work-related barriers and work participation following the CoreDISTparticipation intervention will add new knowledge to meet known challenges regarding early withdrawal from the workforce [4,5,18,19,27]. As CoreDISTparticipation includes information videos about the disease and the possibilities for work-related adaptations for both employers and pwMS, as well as a guide for discussion of such challenges with NAV consultants, these measures can easily be implemented in regular welfare in Norway, as well as adapted to similar health and welfare systems. Thus, this study may meet requests from pwMS for adaptations to increase or maintain their employment status [31], which is essential for HRQoL [5].

Given the positive effects of CoreDISTparticipation on physical activity, this study will add valuable information expanding prior work. So far, it has been difficult to document effects on physical activity [58,59], except for an intervention emphasizing behavioral adaptation [60]. If CoreDISTparticipation proves effective compared to usual care, it will point toward a direction for physiotherapy-led activity highlighting a combination of specific core/balance exercises and high-intensity interval training. Moreover, the study will examine fatigue, balance, postural control, walking, and HRQoL—all well-known barriers to work in this population [30,61]—and will provide a deeper understanding of the relationships between these, which can inform health and welfare services.

Finally, this study will provide objective information about health economic factors related to pwMS with low disability. This includes the utility of the CoreDISTparticipation program compared to usual care, expressed in QALYs, long-term employment status, and work-related costs. Given the high work-related costs associated with pwMS [4,7], this study will offer essential insights to further develop cost-effective models of care and potentially enhance workforce sustainability for this group. Thus, the study addresses the part of the follow-up that represents the highest societal costs for pwMS in Norway [4].

If the novel intervention proves effective compared to usual care, it will offer a low-cost approach to be delivered across sectors and health care levels in both rural and urban settings. CoreDISTparticipation can easily be implemented into routine care as it is integrated into existing health and welfare system structures. Educational materials and training programs for NAV consultants and physiotherapists have been developed, and digital materials to optimize physical functions and physical activity for pwMS are being tested in this trial. The exercise component of the intervention requires low-cost equipment that is typically available in standard physiotherapy practices. Moreover, since the trial involves 4 hospital trusts and 22 municipalities of varying sizes in Norway, the necessary flexibility for implementation in both densely and sparsely populated areas will already be covered. CoreDISTparticpation is the first intervention to introduce a proactive approach to well-known work-related challenges experienced by pwMS. The timing of such support, although in active employment, is so far unexplored within the welfare system.

Additionally, the results from the study may be relevant to inform the follow-up care of other groups of young adults with chronic diseases, particularly in the neurological field. The study will provide the health and welfare sectors with new and highly relevant scientific knowledge that could potentially increase sustained employment and physical activity, which may consequently increase health and HRQoL. Such prospects open for future reduced work-related societal costs and increase in the workforce, which is highly requested by authorities [62].

